(1)	To describe the demographic, social and psychological factors that affect sexual risk behaviors, partner uptake of VCT, family planning intention, infant feeding choices, and HIV serostatus disclosure to sexual partners, among HIV-positive and HIV-negative women attending the Umlazi Section D ANC clinic in Durban, South Africa. 

(2)	To conduct a randomized controlled trial of HIV VCT plus enhanced posttest support as compared to standard HIV VCT among HIV-positive and HIV-negative pregnant women in the Umlazi Section D ANC clinic to determine the independent effect of the intervention on the outcomes listed below, and to determine whether HIV-serostatus to sexual partners influences these intervention effects:
2.1 	Sexual risk of HIV as measured by:  STI incidence (Trichomonas vaginalis, Neisseria gonorrhea and Chlamydia), consistent and correct condom use among HIV-positive and HIV-negative women; and partner uptake of HIV VCT among HIV-positive women.  
2.2. 	Factors that affect mother-to-child transmission of HIV including: acceptance of HIV VCT among HIV-positive and HIV-negative women; acceptance of ARVs, adherence to national infant feeding guidelines, and family planning use among HIV-positive women.
2.3. 	Psychosocial outcomes of PMTCT participation as measured by: perceived social support, emotional distress and partner violence among HIV-positive and HIV-negative women.  
2.4 	With the addition of the legal education and referral component to the intervention study, we will also measure women's awareness of legal rights, awareness of legal recourse, perceived legal needs, uptake of legal assistance and outcome of seeking legal assistance within the 12 month study period. 

(3)	 Additionally, our secondary aim is to compare the following operational outcomes across study arms:  (a) counseling time required; (b) the proportion of women returning for ongoing counseling at 6 and 10 weeks; (c) client's perceived quality of services; (d) the cost of service provision and opportunity costs incurred by clients.
   

Our collaboration includes a multidisciplinary team of researchers from the U.S. and South Africa who will join efforts to test a culturally appropriate and feasible intervention designed to overcome limitations and expand the preventive health benefits of PMTCT programs. Results from this intervention study will be generalizable to other regions of sub-Saharan Africa that are faced with similar challenges related to HIV prevention.

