The second primary aim of the study is to conduct a randomized controlled trial of HIV enhanced post-test support as compared to standard HIV counseling among HIV-positive and HIV-negative women in the Umlazi Section D ANC clinic.  To do this we will randomize 1,495 women at Umlazi Section D ANC in Durban, South Africa to either a comparison or an intervention arm. Women randomized to the comparison arm will receive the standard WHO/CDC HIV pre-and post-test counseling and will have brief follow-up sessions with counselors 6- and 10-weeks postpartum. Women randomized to the intervention arm will receive: 1) a health education video immediately prior to HIV pre-test counseling; 2) pre and post-test counseling sessions that build on the standard protocols by providing more risk reduction counseling, more counseling on disclosure, and PMTCT-related decisions; 3) two additional post-test counseling sessions that coincide with the 6- and 10-week postpartum visits and focus on legal education and referral, partner testing, sexual behavior change and family planning; 4) an active referral to post-test support groups and 6) access to onsite legal support. Women in both arms will be administered a baseline survey at enrolment. Post-intervention assessment will occur at 14 weeks and 9-months post-partum. We will examine the independent effect of the intervention on primary outcomes related to sexual risk transmission of HIV, factors that affect mother-to-child transmission, and psychosocial outcomes of PMTCT participation for women.  We will also examine what influence HIV serostatus disclosure to sexual partners has on these effects.  See Figure 1.    
We have a secondary aim to compare operational outcomes across study arms.   We will compare  counseling time required, proportion of women returning for ongoing counseling at 6 and 10 weeks, clients perceived quality of services and the cost of service provision and opportunity cost incurred by client across the two arms.  This aim will be achieved through analysis of clinic records including counseling log forms and financial records. 

D.2. Study Site and Population

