D.4.6. Tracing Procedures: The following systems are in place at the Clinic to maintain cohort retention and follow up: (1) A well-designed computerized follow-up program to keep track of all scheduled daily appointments and missed appointments together with contact information; (2) Study participants who miss their scheduled appointments are contacted within 24-hours by telephone if they left a telephone contact at enrollment. Approximately, 65% of ANC clients enrolled in previous studies have provided telephone contact information. This first line of contact is a reminder telephone call to the participant directly or to a close contact that is identified by the client, while maintaining confidentiality. (3) They are then given a week before a home visit is attempted if home location was provided by the clients.  Home visits are done by tracers familiar with the residential areas.  For the proposed study we will employ two full-time tracers.  If the participant has changed her address maximum information is gathered (while maintaining confidentiality of the participant) from neighbors and relatives that forms the basis of further contact. (5) A participant is considered lost to follow-up after 3 unsuccessful  attempts of telephone contact, and 2 unsuccesful home-visits.  A similar system for tracing study participants has been utilized in the previous clinical trials implemented at the nearby PMMH, and has resulted in retention rates of higher than 90%, with no adverse events associated with tracing reported.80     

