D.8.1.12. Partner Violence: From our previous research, we found that using specific behavioral events rather than a cover term such as 'physical violence' is more useful for the measurement of violence.  This has been corroborated by violence research from other settings, including South Africa47,110  We will measure sexual and physical violence using an adaptation of the Conflict-Tactic Scale111.  (See Appendix 13)  We adapted this scale for use in the research that we conducted in Tanzania and the scale demonstrated good internal consistency and reliability for physical and verbal abuse in this setting60 .  The modified scale demonstrated good reliability and internal consistency in the eight countries where WHO conducted a study on women's health and gender-based violence and in a South African study conducted by Jewkes112,47.  At baseline we will ask women to recall their experiences with violence during pregnancy and prior to pregnancy. At the post-intervention assessment we measure women's experiences with violence in the 9-month period of time since testing.  We will adhere to WHO ethical and safety guidelines for conducting research on violence against women.  We will have a referral list of social and legal services available to women who report current  violence113.

D.8.2. Secondary Outcomes
D.8.2.1. Length of time for counseling sessions:  Counselors will maintain a counseling log form for every woman in the intervention and the comparison arm.  Among other things reported on this log form, counselors will report the beginning and ending time of each counseling session.  

D.8.2.2 Ongoing counseling: We will monitor the ongoing use of counseling services by women in both arms.  Counselors will record every counseling session that is conducted with clients on the counseling log forms.  Through these counseling logs forms we will also track the number of women who return for counseling with her partner. We will start a separate counseling log for those partners who return to the clinic either on their own for HIV counseling or with their partner.  

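### Return for counselling at 6 and 10 weeks is counted after missed appointments have been traced, so the outcome mixes unprompted return with research tracing and shrinks any arm difference by an unknown factor

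*Protocol*

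**What the plan says.** The Specific Aims (Aim 3) list among the outcomes to be compared across arms "the proportion of women returning for ongoing counseling at 6 and 10 weeks", and D.1 repeats it. Under D.8.2.2 the source is the counselling log: "Counselors will record every counseling session that is conducted with clients on the counseling log forms". D.11 compares the Aim 3 outcomes between arms with contingency tables and chi-square tests, and makes no reference to tracing.

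Both arms have these sessions. D.5.2 and D.7 give the comparison arm 6- and 10-week sessions on infant health, similar in length to those of the intervention arm.

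D.4.6 describes tracing for study participants. The follow-up program is to "keep track of all scheduled daily appointments and missed appointments together with contact information". The first step is a call: "Study participants who miss their scheduled appointments are contacted within 24-hours by telephone if they left a telephone contact at enrollment". On coverage it says: "Approximately, 65% of ANC clients enrolled in previous studies have provided telephone contact information". If the call does not succeed, a home visit is attempted after a week, provided the woman gave a home location. Two tracers are to be employed full time. The section makes no exception for the 6- and 10-week visits. Neither D.4.6 nor D.8.2.2 says whether a session that took place only after tracing counts as a return.

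**The concern.** The outcome is meant to show whether the enhanced model brings women back for counselling. Tracing is a research procedure that acts on exactly the event being counted, in both arms. A woman who came after a tracer contacted her is logged in the same way as one who came unprompted.

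Two consequences follow. The reported return rate is higher than a clinic without tracers would see, which matters for an outcome intended to inform service delivery. And if tracing works about equally well in both arms, the arms move closer together. A null result on Aim 3(b) could then mean that the model does not improve return, or that tracing brought back the non-attenders in both arms. The data as described could not tell these apart.

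**Working it through.** **The protocol's own figures.** No sample size or power is stated for return at 6 and 10 weeks. The only sample-size table (Table 3, for STI incidence) reproduces exactly with a pooled-variance two-proportion formula, two-sided α = 0.05, an assumed power of 80% (no power is stated) and no continuity correction: 22% v 13% gives 279 per arm, and 18% v 10% gives 295. The same normal approximation is used below.

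**Inputs from the protocol.** Enrolment is 1,495 (D.9.3), so about 747 per arm if allocation is equal, which is assumed. The HIV-positive stratum is 279 per arm (D.9.3), and D.11 says analyses are done separately by serostatus. Telephone coverage was about 65% in previous studies (D.4.6).

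**Inputs that are assumptions.** The protocol gives neither the unprompted return rate nor the success of tracing. For illustration, unprompted return is taken as 60% v 72%. The share r of non-attenders recovered by tracing is varied and taken as equal in both arms.

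**Attenuation.** The observed proportion is p′ = p + r(1 − p). The observed difference is therefore

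p₂′ − p₁′ = (1 − r)(p₂ − p₁).

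**Plausible r from calls alone.** With 65% coverage and an assumed call success of 30% or 50%, r = 0.65 × 0.30 ≈ 0.20 or 0.65 × 0.50 = 0.325. If the 65% applies to non-attenders, calls alone cannot exceed r = 0.65. Home visits add to r, but no success rate is given for them.

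**Power.** Power = Φ[(d − 1.96·se₀)/se₁], with se₀ = √(2p̄(1 − p̄)/n) and se₁ = √((p₁(1 − p₁) + p₂(1 − p₂))/n).

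Example at r = 0.5, n = 747: the proportions are 0.80 and 0.86, p̄ = 0.83, se₀ = 0.01944, se₁ = 0.01937. Then (0.06 − 1.96 × 0.01944)/0.01937 = 1.13, so power is 87%.

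| r | Observed return | Difference (points) | Power, 747 per arm | Power, 279 per arm |
|---|---|---|---|---|
| 0 | 60.0% v 72.0% | 12.0 | >99% | 85% |
| 0.2 | 68.0% v 77.6% | 9.6 | 99% | 72% |
| 0.325 | 73.0% v 81.1% | 8.1 | 96% | 62% |
| 0.5 | 80.0% v 86.0% | 6.0 | 87% | 47% |
| 0.8 | 92.0% v 94.4% | 2.4 | 45% | 20% |

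The 279 is the number the protocol needs at the 9-month assessment. More HIV-positive women may be available at 6 and 10 weeks, so the last column is on the low side for that stratum.

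**The case against.** Several points on the other side are sound.

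- **Tracing is conditional.** A reader might infer that every woman who misses an appointment is both telephoned and visited. D.4.6 does not say so: the call needs a number, and the visit needs a location and a week's delay.
- **The size is unknown.** A reader might infer that an arm difference would be largely erased. That needs r well above one half. With calls alone at 30–50% success, about two thirds to four fifths of the difference remains, and power with all enrolled women stays at 96% or more.
- **The retention figure does not fix r.** D.4.6 reports retention above 90% for a similar tracing system. That is overall retention in earlier trials at a nearby hospital, not attendance at a given visit.
- **Tracing is not the only driver.** The sessions coincide with infant immunisation in both arms (D.6), and planning to attend immunisation visits is an eligibility criterion (D.4.1). It goes too far to say that the outcome measures only tracing.
- **Some of this could sit in an analysis plan.** Visit windows for a secondary operational outcome often do, and the follow-up program already tracks missed appointments.

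The first four limit the size of the claim but leave its direction. The last stands in part. However, the protocol itself sets both the counting rule and the tracing rule that acts on it. Whether a session followed a tracing contact must also be recorded when it happens. The logs are described without such a field, and if contact dates are not linked to appointments, no later plan can recover unprompted return.

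**Conclusion.** The point holds in a limited form. As written, the return outcome mixes unprompted attendance with attendance after research tracing. It overstates the rate a clinic without tracing would see, and it attenuates an arm difference by (1 − r) if tracing is equally effective in both arms.

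The direction follows from the design, but the size cannot be fixed from the document. On the assumed 60% v 72%, the loss runs from slight (9.6 of 12 points kept at r = 0.2) to severe (2.4 points kept at r = 0.8). Within the HIV-positive stratum, even r = 0.325 takes power from 85% to 62%. If tracing success differed between arms, the bias would no longer be a simple shrinkage.

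Only Aim 3(b) is affected. A reader might infer that the primary comparisons or the sample size are undermined. Nothing here supports that, since retention for the 14-week and 9-month assessments is a proper use of tracing.

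**What to change.** In D.8.2.2, define return at each of the 6- and 10-week visits as attendance by one fixed cut-off that applies to all women, whether or not they left a telephone number, and that falls before tracing starts. An example is attendance on the scheduled date, or before the 24-hour call is due. State that no tracing contact is made before that cut-off.

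The cut-off should not be each woman's own first tracing contact. Women with a number are called within a day, while those without one are first approached about a week later. A woman with a telephone who came two days late would then count as not returned, and one without a telephone who came five days late would count as returned, so the outcome would depend on telephone access.

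Take the outcome from the computerised follow-up program in D.4.6, and record the date of each tracing contact against the appointment concerned. Report total attendance, including traced women, separately by arm as a measure of intervention delivery.

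The cost is one definition and one dated field in an existing system; the tracing steps, visits and sample size do not change. The downside is that women who come late but unprompted count as not returned, in both arms alike, so the stated rate will be lower.

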D.3. Ethnographic Research: To answer our first specific aim we will conduct qualitative interviews with women from the ANC clinic and the male partners of ANC clients.  The purpose of this ethnographic data is to describe factors that affect key study behaviors such as sexual risk behavior, ARV uptake, infant feeding choices, family planning intentions, partner testing and disclosure of serostatus to sexual partners from the perspective of women and their male partners.  This data will help inform the intervention and refine measures used in the quantitative instrument.  All in-depth interviews will be conducted in a private room in the ANC clinic, audiotaped, transcribed, translated and computerized for data analysis.  We will conduct qualitative research to: (1) Describe the factors that influence women's decisions about ARV acceptance, infant feeding, family planning, condom negotiation and to specifically assess what role HIV serostatus disclosure to partners plays with regard to each of these decisions.  We will conduct 64 in-depth interviews with women from the ANC clinic who have returned for the 6-week post-partum visit.  Among the 64 women we will purposively select both HIV-positive women and HIV-negative women to discuss the above topics.  To be eligible for these interviews women must be a client at the ANC clinic, must have been tested for HIV in an earlier ANC visit and must be able to identify a primary partner, which we will define as someone they have been with for at least 6-months.  (2) Describe male attitudes toward and determinants of participation in MTCT and uptake of HIV VCT: We will conduct 16 in-depth interviews with male partners of ANC clients. To ensure the safety of women, we will recruit these male partners through self-referrals from the women.  Ethnographers will ask women who report that they have shared their HIV test results with their partner and have not experienced negative outcomes as a result of this disclosure whether they would be willing to refer their partner to the clinic for an interview. (3) Pilot test the video:  We will pilot test the video with HIV-positive and HIV-negative women from the Umlazi Section D ANC clinic. We will conduct 5 focus group discussions (FGD) with 6-8 women each. Women who have been counseled and tested for HIV in the Umlazi Section D ANC clinic within the last one month will be recruited for each FGD.  The groups will watch the entire video in a private room within the ANC clinic.  After viewing the video the FGD facilitator will facilitate a discussion about the language and the content of the video. (4) Pilot test the counseling sessions: Through our pilot study among women in a VCT clinic we developed counseling tools, including the use of role-play scenarios and a disclosure-related violence structured counseling tool (described in section D.5.2.4).  For the purpose of the proposed study we will tailor these tools to antenatal women. We will use these tools in our counseling sessions, and will pilot our counseling program with 5 women in its entirety. Soon after the pilot sessions, women will be asked about acceptability, clarity and relevance of the counseling session; (5) Pilot test the interviewer administered questionnaire: Interviewer administered questionnaires (IAQ) has been the standard practice for other clinical trials conducted by the collaborating group at University of KwaZulu-Natal.  We will pilot our interviewer administered baseline survey 2 different ways. First, we will conduct cognitive interviews with 5 women to evaluate our baseline survey. During these interviews, we will ask each woman the questions within each section of the baseline survey. At the end of each section, we will ask each woman a series of questions about the content of the section in order to assess their understanding of each question, to determine whether the response categories are sufficient, and to evaluate whether questions need to be added, deleted or altered. Following the cognitive interviews, we will make any necessary changes to the baseline survey instrument. We will then pilot the baseline survey in its entirety with 15 women from the Umlazi Section D Clinic.

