
 D.5.2.4. A structured discussion regarding disclosure-related violence:  We want to insure that we respect women's independent choices regarding disclosure and insure that we provide women with counseling that can help minimize any negative outcomes they may face as a result of disclosure.  HIV counseling in both the intervention and the comparison arm of this trial will be client-centered, which means that the role of the counselor is to enable and support personal decisions related to disclosure.  Counselors will use a structured discussion tool to help women assess their risk for physical harm following disclosure.  We developed this tool based on the factors that were associated with disclosure-related violence in our earlier research among women in the HIV VCT clinic in Dar es Salaam.  The counseling tool consists of 5 questions that are meant to prompt discussion about the possibility of disclosure-related violence between the counselors and their clients.  The questions include: (1) Is your partner aware that you will be tested for HIV?  (2) If you told your partner you tested positive for HIV do you think he would react supportively?  (3) Are you afraid of how your partner will react if you share your HIV test results with him?  (4) Has your partner ever physically hurt you?   (5) Do you think that your partner may physically hurt you if you tell him that you have tested for HIV and your HIV test results are positive?  Counselors will support women's decisions to disclose if they answer positively or negatively to question 1, positively to question 2 and negatively to questions 3-5.  If women answer negatively to question 2, and positively to any of the following questions, 3-5, then counselors will proceed with caution and explore in more depth women's risk of disclosure related violence.  If they determine that the risk is great, they may explore alternative options including opting not to disclose, deferring disclosure to a time when women's safety can be insured or developing a plan for mediated disclosure in which the women either brings the partner to the clinic to disclose in the presence of a counselor or identifies a trusted family member or friend who can be present with the woman when she shares her HIV test results with her partner.  If women answer negatively to question 2 and positively to questions 3-5, regardless of how they answered question 1, then counselors will explore these alternative options for disclosure.   In the feasibility study we conducted in Tanzania, we trained counselors to use this counseling tool and they reported that they were able to implement it as trained without any difficulty.  

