b.	Counseling Observations: The staff psychologist will be responsible for observing 5% of the patient's visits at baseline, 6 weeks and 10 weeks. These sessions will be randomly sampled. The staff psychologist will have a checklist to verify that the content of the session adheres to the protocol. The psychologist will also evaluate the quality of the nurse's counseling. These evaluations will be used to maintain quality of care in delivery of services across both the control and intervention arms. 
c.	Exit Interviews: The survey interviewers will be responsible for conducting exit interviews with 5% of the participants following the baseline, 6 week and 10 week sessions. These sessions will be randomly sampled. These interviews will address perceived quality of services received and they will be used to maintain quality of care or improve quality of care as needed across both the control and intervention arms. 

D13.2.2 Quality Control IN DATA MANAGEMENT
a.	The Project Coordinator will be responsible for auditing 5% of the patient's medical charts at the baseline, 6 week and 10 week visit for protocol compliance. These charts will be randomly selected.  The audit will involve a comparison between the woman's antenatal card and the infant's road to health card with our Medical Extraction Form. The nurses will extract a number of pieces of valuable information from these cards onto our Medical Extraction Form . We want to ensure that the nurses are reliably extracting information from these two sources into our Medical Extraction Form.
b.	The Project Coordinator will also be responsible for validating 5% of data captured by the data capturer.  She will verify data captured on the database against the Medical Extraction Forms.

D.14. Data Safety and Monitoring Plan: 

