Voluntary choice regarding disclosure: We recognize the potential risks associated with HIV serostatus disclosure to sexual partners among women.  We have conducted prior research studies on the associations between HIV and violence against women and we have reviewed the literature extensively to further understand the positive and negative outcomes of disclosure for women.  There is some evidence to suggest that women who disclose HIV test results to their partners are at risk for experiencing negative reactions, including physical violence.  While the rates of HIV serostatus disclosure related violence are relatively low in the U.S. (between 0.5-4%) the risks of violence following disclosure among women in sub-Saharan Africa is higher (3.5%-14.6%).  The potential risks associated with disclosure have to be weighed against the possible individual and public health benefits of disclosure.  Expanded awareness of risk that comes with disclosure may enable couples to make informed choices about behavior change and reproduction that may ultimately lower the incidence of HIV.  There are also risks associated with not disclosing HIV test results with a sexual partner, including the risk of transmission to a partner and anxiety associated with concealing this information from a partner.  We have developed a counseling approach that is designed to help women more carefully weigh the risks and benefits of disclosure.   Through the intervention that we are testing in this proposal women will spend more time with the counselors discussing disclosure.  The HIV counseling will be client-centered, which means that the role of the counselor is to enable the client to make independent decisions related to disclosure.  Counselors will use a structured discussion counseling tool to help women assess their risk for physical harm if they disclose HIV positive test results to their partner.  We developed this tool based on the factors that were associated with disclosure-related violence in our earlier research among women in the HIV VCT clinic in Dar es Salaam.  The details of this screening tool have been described in section D.5.2.4.  

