Women who participate in this study may be exposed to some psychosocial risks related to: 1) Negative outcomes of disclosure:  It is possible that women who share HIV test results with their sexual partners will experience negative reactions.  This risk is one that all women in the ANC clinic face, regardless of enrollment in this study.  We will carefully train the HIV counselors to assess whether it is safe for women to share HIV test results with her sexual partners.  The enhanced counseling is designed to help women carefully weigh the costs and benefits to disclosure.  Counselors use a structured discussion counseling tool with to help women assess the risk of violence following disclosure.  If women report a history of violence, anticipate negative reactions from their partner when they disclose and still intend to disclose, counselors will actively encourage women to consider alternative options for disclosing, including postponing disclosure until a time when their safety can be insured, or considering a mediated form of disclosure in which they bring their partner to the clinic to disclose in the presence of a counselor, or they identify a trusted family member or friend who can be with them when they disclose to their partner at home.  2) Precipitation of emotional crisis:  It is possible that the qualitative and survey interviews will precipitate an emotional crisis among women who have not had the opportunities to talk about these emotionally charged topics in the past.  To address this risk the interviewers will be trained to respond empathetically to the women.  However, since interviewers are not trained counselors, they will also be trained to refer women who need additional support to the HIV counselors in the clinic.  If the HIV counselors identify women who express psychological needs beyond those that they are trained to handle, they will refer these clients to the Psychologists and Psychiatrists at PMMH.  The Psychologists and Psychiatrists that staff PMMH provide ongoing psychological support for all clients.  These services will be available to all women in this trial.  An active referral mechanism to these support groups will be part of the intervention protocol tested in this trial.    

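### The violence-risk tool requires deeper exploration only when the woman does not expect support, so its answer rules give no route for 8 of 16 answer patterns

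*Protocol*

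**What the plan says.** D.5.2.4 describes "5 questions that are meant to prompt discussion about the possibility of disclosure-related violence". In short, question 1 asks whether the partner knows about the test, question 2 whether she expects support if positive, question 3 whether she fears his reaction, question 4 whether he has ever hurt her, and question 5 whether he may hurt her if told. Three rules follow:

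- **Support.** Counselors support a decision to disclose, whatever the answer to question 1, if she answers "positively to question 2 and negatively to questions 3-5".
- **Caution.** "If women answer negatively to question 2, and positively to any of the following questions, 3-5, then counselors will proceed with caution" and look further into the risk of violence. If that risk is judged great, they may discuss not disclosing, deferring, or mediated disclosure.
- **Alternatives.** If question 2 is no and questions 3 to 5 are yes, counselors explore those alternatives.

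E. Human Subjects, Description of risks and strategies to minimize risk, adds a further rule: "If women report a history of violence, anticipate negative reactions from their partner when they disclose and still intend to disclose, counselors will actively encourage" other ways of disclosing. It also promises: "We will carefully train the HIV counselors to assess whether it is safe for women to share HIV test results".

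Other provisions bear on the first post-test session:

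- Table 1 (intervention components by arm) gives the tool only to HIV-positive intervention women. It offers mediated disclosure to all intervention women.
- D.5.2.3 presents disclosure approaches to women who choose to disclose and for whom that is safe.
- D.13.2.1 has 5% of visits observed: "The staff psychologist will have a checklist to verify that the content of the session adheres to the protocol". The psychologist also rates counseling quality.

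**The concern.** The tool exists to pick out women for whom disclosure may be dangerous. D.5.2.4 says that it was built from factors associated with disclosure-related violence in the team's earlier research. Fear, past harm and expected harm are three of the four answers that determine the route. With AND in the trigger, none of the three, alone or together, leads to required exploration once the woman says that she expects support.

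The clearest case is a woman whose partner has already hurt her, who expects him to be supportive, is not afraid and does not expect harm. The support rule does not cover her, so the text does not treat her as cleared. The caution rule does not cover her either.

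This is a matter of participant safety. E. Human Subjects lists the tool among the strategies against negative outcomes of disclosure and calls it a screening tool: "The details of this screening tool have been described in section D.5.2.4". It also cites violence after disclosure in 3.5% to 14.6% of women in studies from sub-Saharan Africa. The 6- and 10-week postpartum sessions, and the reporting of harms, come after she may already have disclosed.

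**Working it through.** The protocol gives no figure to reproduce, so the check is an enumeration.

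**Inputs.** The three rules of D.5.2.4 and the rule in the risk section of E. Human Subjects. Question 1 does not change the route, so it can be left out. That leaves questions 2 to 5, each yes (Y) or no (N): 2^4 = 16 patterns, written in the order 2-3-4-5.

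**Step 1: apply D.5.2.4 as written.**

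| Rule | Condition | Patterns | Count |
|---|---|---|---|
| Support | 2 yes; 3, 4, 5 all no | YNNN | 1 |
| Caution | 2 no AND any of 3–5 yes | NYNN, NNYN, NNNY, NYYN, NYNY, NNYY, NYYY | 7 |
| Alternatives | 2 no; 3, 4, 5 all yes | NYYY (already under caution) | 0 further |
| No route | the rest | YYNN, YNYN, YNNY, YYYN, YYNY, YNYY, YYYY, NNNN | 16 − 1 − 7 = 8 |

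Seven of the eight pair an expectation of support with at least one of fear, past harm or expected harm. The eighth, NNNN, is a lower-risk pattern: no support expected, but no fear, history or expected harm.

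**Step 2: apply the risk section to the eight.** It needs a history of violence (question 4 yes) and an anticipated negative reaction.

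- Broad reading of the second condition (question 2 no, or question 3 or 5 yes): it reaches YYYN, YNYY and YYYY, so 3 of 8. It also requires that she still intends to disclose.
- Narrow reading (question 2 no only): it reaches 0 of 8.

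On the broad reading 8 − 3 = 5 remain:

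- YNYN: hurt before, expects support, not afraid, expects no harm.
- YNNY and YYNY: no history, expects support, but says he may hurt her.
- YYNN: no history, expects support, but afraid.
- NNNN.

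**Step 3: check whether the general safeguards fill the gap.** Offering mediated disclosure gives her an option without exploring her risk. D.5.2.3 depends on disclosure being safe, but the tool's rules do not say how to classify these women. Training in assessing safety and observation of quality may lead a counselor to explore. Neither requires it for these answers.

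**Step 4: replace AND by OR.** Caution applies if question 2 is no OR any of 3–5 is yes: 16 − 1 = 15 patterns. Support stays at 1, and 15 + 1 = 16 leaves none without a route.

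**The case against.** The strongest reply is that this is a conversation aid inside client-centered counseling, not a scoring algorithm. A woman who says that her partner has hurt her has already opened the subject. Counselors are trained by a clinical psychologist and certified (D16), and the observing psychologist rates quality as well as adherence. This stands as far as it goes: judgment may well fill the gap in practice. But D.5.2.4 goes beyond prompts and writes answer-based rules. A session that stopped at those rules for one of the eight patterns would not contradict them.

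A reader might infer that these women get no protection at the first post-test session, or that the protocol clears them to disclose. The documents do not support either. Mediated disclosure is offered regardless of answers, disclosure approaches are tied to safety, and the support rule excludes all eight patterns. A reader might also take 8 of 16 to mean half of the women. Patterns are not women, and some of them combine answers that look inconsistent. The 3.5% to 14.6% range and the 40% planning rate for physical violence over 9 months in HIV-positive women (Table 4) do not measure how often these combinations occur.

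It can also be said that AND may have been deliberate, and that OR flattens the triage by sending 15 of 16 patterns to caution. The research behind the tool is not set out in enough detail to judge intent. The flattening is real at the first step, but the third rule and the counselor's discretion keep a graded response. Caution adds discussion and blocks nobody from disclosing.

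**Conclusion.** The point holds for the answer-based routing rules of D.5.2.4. They require in-depth exploration in 7 of 16 patterns and leave 8 without a route. The risk section reaches at most 3 of these, so at least 5 remain. The general safeguards apply to these women, but none requires deeper exploration of their violence risk.

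The count rests on reading the rules literally, treating each question as yes or no, and reading the third rule as needing yes to all of questions 3 to 5. A looser third rule would still require question 2 to be no and at least one of 3–5 to be yes, so the 8 would not change. The number of women affected cannot be derived from the protocol.

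The point concerns HIV-positive women in the intervention arm only. It does not touch sample size, power or error rates. It should be fixed because it bears on safety and the remedy is cheap.

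**What to change.** In D.5.2.4, change the caution trigger to: a negative answer to question 2 OR a positive answer to any of questions 3–5. Keep the support rule, the third rule and the counselor's discretion over alternatives as they are.

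The natural moment is the adaptation already planned in D.3: "For the purpose of the proposed study we will tailor these tools to antenatal women". That section also plans to pilot the full counseling program with 5 women. Carry the same wording into the operations manual, counselor training and certification (D16) and the observation checklist (D.13.2.1).

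The edit is one word in the protocol plus matching text in those materials. It needs no extra visit, staff or data. The downside is a somewhat longer discussion for some HIV-positive intervention women, within a session where D.5.2.3 already adds 10 to 15 minutes for disclosure. The protocol does not allow the extra time to be quantified; the pilot can show whether it fits.
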